### **9.3.8 Visit 2: Baseline (day 0)**

- Vital signs
- Full lab tests
- LCT
- PDQ-39
- ESS
- BDI
- SAS
- NMSQuest
- LEDD

### **9.3.9 Visit 3: Treatment (day 1 - this visit takes place at the CI Bern)**

- Vital signs
- Full lab tests
- MSD Infusion of TLN
- Blood collections for PK analysis
- MDS-UPDRS (Part III before the infusion; Part I, II and IV during the infusion; Part III again after the infusion)
- AE recording

### **9.3.10 Visit 4 – 7: PK (days 2 to 5 - these visits take place at the CI Bern)**

- Blood collections for PK analysis
- AE recording

### **9.3.11 Visit 8 – 14: Treatment (days 8, 15, 22, 29, 36, 43 & 50)**

- Vital signs
- Full lab tests
- MSD infusion of TLN
- MDS-UPDRS (Part III before the infusion; Part I, II and IV during the infusion; Part III again after the infusion)
- NMSQuest
- LEDD
- AE recording

### **9.3.12 Visit 15: Final assessment (7 days after last TLN infusion)**

- Clinical assessment (including physical medical and neurological exam, height and weight).
- Vital signs

- MoCA
- Full lab tests
- LCT
- MDS-UPDRS
- PDQ-39
- ESS
- BDI
- SAS
- NMSQuest
- LEDD
- AE recording

9.3.13 Visit 16: Follow-up (28 days after last TLN infusion)

- Clinical assessment (including physical medical and neurological exam, height and weight).
- Vital signs
- Full lab tests
- MDS-UPDRS
- LEDD
- AE recording

**After dose escalation: optional further treatment**

9.3.14 Visit 0: "Re-consent" (day 0)

- Explanation of the option of treatment prolongation (15 min).  
Patient information is handed out in writing. This procedure might also take place during the final assessment or follow-up visit of part 1. Then this visit will not take place.

9.3.15 Visit 1-8: Treatment (day 1, 8, 15, 22, 29, 36, 43 & 50)

- Vital signs
- Full lab tests
- MSD Infusion of TLN
- MDS-UPDRS (Part III before the infusion; Part I, II and IV during the infusion; Part III again after the infusion)
- NMSQuest
- LEDD
- AE recording

9.3.16 Visit 9: Final assessment (7 days after last TLN infusion)

- Clinical assessment (including physical medical and neurological exam, height and weight).
- Vital signs
- MoCA
- Full lab tests
- LCT
- MDS-UPDRS
- PDQ-39
- ESS
- BDI
- SAS
- NMSQuest
- LEDD
- AE recording

9.3.17 Visit 10: Follow-up (28 days after last TLN infusion)

- Clinical assessment (including physical medical and neurological exam, height and weight).
- Vital signs
- Full lab tests
- MDS-UPDRS
- LEDD
- AE recording

## 10. SAFETY (DRUG STUDY)

As sponsor of this trial, InnoMedica has established a framework of quality assurance which encompasses responsibilities and documents (e.g., SOPs) which fully cover safety aspects. During the entire duration of the trial, all AEs and all serious adverse events (SAEs) are collected, fully investigated and documented in source documents and case report forms (CRFs). Trial duration encompassed the time from when the participant signs the informed consent until the last protocol-specific procedure has been completed, including a safety follow-up period of 28 days. The SMP provides detailed information.

### 10.1 Definition and assessment of (serious) adverse events and other safety related events

An **Adverse Event (AE)** is any untoward medical occurrence in a patient or a clinical investigation participant who was administered a pharmaceutical product and which does not necessarily have a causal relationship with the study procedure. An AE can therefore be any unfavourable and unintended sign (including an abnormal laboratory finding), symptom, or disease temporally associated with the use of a medicinal (investigational) product, whether or not related to the medicinal (investigational) product.

AEs (and SAEs) will be documented by the PI and collected and documented in the DB.

A **Serious Adverse Event (SAE)** is classified as any untoward medical occurrence that:

- results in death,
- is life-threatening,
- requires in-patient hospitalization or prolongation of existing hospitalisation,
- results in persistent or significant disability/incapacity, or
- is a congenital anomaly/birth defect.

In addition, important medical events that may not be immediately life-threatening or result in death, or require hospitalisation, but may jeopardise the patient or may require intervention to prevent one of the other outcomes listed above should also usually be considered serious.

SAEs should be followed until resolution or stabilisation. Participants with ongoing SAEs at study termination (including safety visit) will be further followed up until recovery or until stabilisation of the disease after termination.

In order to standardise all AEs, they will be coded according to the Medical Dictionary for Regulatory Activities (MedDRA). Adverse events and SAEs will be summarized by body system and preferred term based on the Medical Dictionary for Regulatory Activities (MedDRA).

A **Suspected Unexpected Serious Adverse Reaction (SUSAR)** will be assessed based on possible AEs.

As there are no data for TLN in humans available, the following list of possible AEs is based on literature from clinical trials in which GM1 was applied in different galenic forms and dosages. If any of these AEs would appear in the trial, they would be judged as "expected" AEs.

- Local pain
- Pruritus
- Vasovagal reaction
- Urinary tract infection
- Mild head soreness
- Nocturnal confusion
- Exfoliative dermatitis
- Mild meningitis
- Slightly increased CSF/serum albumin
- Increase in systolic blood pressure
- Hyperreflexia
- Transient rash
- Conjunctivitis
- Modest elevation in cholesterol and triglycerides
- Erythema
- Hyperthermia
- Shivering
- Confusional state

- Severe allergic reaction
- Polyradiculopathy
- GBS
- Haematuria
- Hyperlipidaemia (Cholesterol, triglycerides, Apolipoprotein B)
- Swelling nodule
- Bleeding/hematoma
- Urticaria
- Induration
- Asthenia
- Worsening of PD symptoms
- Anastomotic ulcer/stomach cancer
- Unsteadiness
- Overactivity

#### Assessment of Causality

Both Investigator and sponsor make a causality assessment of the event to TLN, based on the criteria listed in the ICH E2A guidelines:

| Relationship                                                                            | Description                                                                                                               |
|-----------------------------------------------------------------------------------------|---------------------------------------------------------------------------------------------------------------------------|
| Definitely                                                                              | Temporal relationship
Improvement after dechallenge*
Recurrence after rechallenge
(or other proof of drug cause) |
| Probably                                                                                | Temporal relationship
Improvement after dechallenge
No other cause evident                                          |
| Possibly                                                                                | Temporal relationship
Other cause possible                                                                             |
| Unlikely                                                                                | Any assessable reaction that does not fulfil the above conditions                                                         |
| Not related                                                                             | Causal relationship can be ruled out                                                                                      |
| *Improvement after dechallenge only taken into consideration, if applicable to reaction |                                                                                                                           |

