## **1.6 Internal Monitoring Committee (IMC)**

The IMC is the executive board concerning decisions during the trial (e.g., dose escalation procedure) and consists of the PI, the manager medical affairs, and an external Medical Doctor as an independent medical monitor. The sponsor guarantees the independence of the later as he/she has an important role within the IMC. Every discussion/decision of the IMC will be documented and filed in the trial master file (TMF). Decisions to pursue the trial for each patient will be taken unanimously by the three members. This guarantees that the external member's opinion will have the same value as of the other members.

In principle, the IMC will meet on a weekly basis during the treatment phase in order to evaluate all safety data reported until that timepoint. All data will be verified and SAEs re-assessed before.

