### 7.3 Criteria for withdrawal / discontinuation of participants

Patients will be withdrawn from the trial for any of the below listed reasons:

- Unacceptable toxicity as described in section **8.3 Dose modifications**
- Protocol treatment has to be delayed for more than 3 weeks
- Patient refuses further treatment
- Patient becomes pregnant
- Medical judgement by the treating physician
- Severe non-compliance with the trial protocol

For data and follow-up, see section **8.5 Data Collection and Follow-up for withdrawn participants**.

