### 8.3 Dose modifications

Dose modifications are foreseen in cases where a causal relationship to the treatment with TLN cannot be excluded. A causal relationship in this trial is defined as a possible, probable or definite linkage to TLN according to ICH E2A (for more details see section **10. Safety**).

Any grade 4 event with causal relationship to treatment is judged as unacceptable toxicity and will lead to a stop of treatment without resuming the treatment in the affected patient.

Any SAE leads to a treatment stop for the affected patient with the following exception:

- if there is no causal relationship to TLN and the definition for an SAE is fulfilled **uniquely due to an overnight hospital stay (1 night) for an otherwise not severe or serious medical problem**, the patient can continue study participation.

In case of an SAE with no causal relationship to TLN, the patient will be replaced.

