#### Part 1 – Dose escalation:

| Causality            | Intensity   | Resolution until next infusion | Next patient added/ Dose increase                                                                                                         |
|----------------------|-------------|--------------------------------|-------------------------------------------------------------------------------------------------------------------------------------------|
| (unlikely/unrelated) | grade 1 - 3 | yes/no                         | yes                                                                                                                                       |
| Possible             | grade 1     | yes                            | yes                                                                                                                                       |
| Possible             | grade 1     | no                             | yes                                                                                                                                       |
| Possible             | grade 2     | yes                            | yes                                                                                                                                       |
| Possible             | grade 2     | no                             | Delay till resolution (maximum of 3 weeks), then rechallenge at same dose level, if re-occurrence stop treatment for the affected patient |
| Possible             | grade 3     | yes/no                         | no (stop treatment for the affected patient but others to continue)                                                                       |
| Probable/definite    | grade 1     | yes/no                         | yes                                                                                                                                       |
| Probable/definite    | grade 2     | yes                            | yes                                                                                                                                       |
| Probable/definite    | grade 2     | no                             | no (stop treatment for the affected patient but others to continue)                                                                       |

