#### Part 2 – Dose consolidation:

| Causality            | Intensity   | Resolution until next infusion | Dose repeat                                                                                                                          |
|----------------------|-------------|--------------------------------|--------------------------------------------------------------------------------------------------------------------------------------|
| (unlikely/unrelated) | grade 1 - 3 | yes/no                         | yes                                                                                                                                  |
| Possible             | grade 1     | yes                            | yes                                                                                                                                  |
| Possible             | grade 1     | no                             | yes                                                                                                                                  |
| Possible             | grade 2     | yes                            | yes                                                                                                                                  |
| Possible             | grade 2     | no                             | Delay till resolution (maximum of 3 weeks), then rechallenge at same level, if re-occurrence stop treatment for the affected patient |

|                   |         |        |                                                                     |
|-------------------|---------|--------|---------------------------------------------------------------------|
| Possible          | grade 3 | yes/no | no (stop treatment for the affected patient but others to continue) |
| Probable/definite | grade 1 | yes/no | yes                                                                 |
| Probable/definite | grade 2 | yes    | yes                                                                 |
| Probable/definite | grade 2 | no     | stop (for the affected patient but others to continue)              |
| Probable/definite | grade 3 | yes    | stop (for the affected patient but others to continue)              |
| Probable/definite | grade 3 | no     | stop (for the affected patient but others to continue)              |

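### Read as printed, the causality table drops a persistent grade 2-3 event with no other possible cause to 'Unlikely', so the written dosing rule is milder than for the same event with a competing cause

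*Protocol*

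**What the plan says.** Section 10.1 (Assessment of Causality) defines five classes. Every class from 'Possibly' upwards needs a temporal relationship. The further conditions are:

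- **Definitely:** improvement after dechallenge, plus recurrence on rechallenge or other proof that the drug is the cause.
- **Probably:** improvement after dechallenge, with no other cause evident.
- **Possibly:** another cause is possible.
- **Unlikely:** "Any assessable reaction that does not fulfil the above conditions".
- **Not related:** causality can be ruled out.

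A footnote adds: "Improvement after dechallenge only taken into consideration, if applicable to reaction". Its asterisk is printed on the 'Definitely' row only.

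Section 8.3 opens with a principle: "Dose modifications are foreseen in cases where a causal relationship to the treatment with TLN cannot be excluded". It then narrows this: "A causal relationship in this trial is defined as a possible, probable or definite linkage to TLN according to ICH E2A". For unlikely or unrelated events of grade 1 to 3, resolved or not, the Part 1 matrix allows the dose increase and the Part 2 matrix allows the dose repeat. For a 'Possible' unresolved grade 2 event, Part 1 says "Delay till resolution (maximum of 3 weeks), then rechallenge at same dose level" and Part 2 says "Delay till resolution (maximum of 3 weeks), then rechallenge at same level". A 'Possible' grade 3 event stops the affected patient in both parts.

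**The concern.** Finding no competing explanation should strengthen the case against the drug. In this table it can weaken the rating. An event that has not improved misses both higher classes. If no other cause is possible, it misses 'Possibly' as well and lands in the residual class, which 8.3 does not count as causal. The presence of an alternative explanation is what secures the protective action.

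This matters because section 6.1.1 ties the individual stop of escalation to the 8.3 matrix, in a first-in-human trial with three escalation patients. It also contradicts the opening sentence of 8.3: causality has not been excluded for such an event, yet no dose modification follows.

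**Working it through.** The plan gives no figure to reproduce, so the check reads the two sections against each other.

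**Step 1. Classify the event.** Inputs are the table and footnote in 10.1. Hold fixed: temporal relationship present, first occurrence (so no rechallenge), no other proof. Vary improvement (yes, no, not applicable) and whether another cause is possible: 3 x 2 = 6 cells.

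| Cell | Improvement | Other cause possible | Footnote on 'Definitely' only, as printed | Footnote also on 'Probably' |
|---|---|---|---|---|
| 1 | yes | no | Probably | Probably |
| 2 | yes | yes | Possibly | Possibly |
| 3 | no | no | **Unlikely** | **Unlikely** |
| 4 | no | yes | Possibly | Possibly |
| 5 | not applicable | no | **Unlikely** | Probably |
| 6 | not applicable | yes | Possibly | Possibly |

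'Unlikely' results in 2 of 6 cells as printed, and in 1 of 6 if the footnote also covers 'Probably'. Cell 3 remains under both. It leaves 'Unlikely' only if the footnote covers 'Probably' and a reversible event that has not improved yet is treated as one to which dechallenge does not apply. The event is then 'Probably' and the inversion disappears.

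**Step 2. Map cells 3 and 4 to the 8.3 matrices.** An event without improvement is unresolved, so the unresolved rows apply.

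| Part | Grade | Cell 3 ('Unlikely') | Cell 4 ('Possibly') | Milder for cell 3? |
|---|---|---|---|---|
| 1 | 1 | increase | increase | no |
| 1 | 2 | increase | delay, then rechallenge | yes |
| 1 | 3 | increase | stop patient | yes |
| 2 | 1 | repeat | repeat | no |
| 2 | 2 | repeat | delay, then rechallenge | yes |
| 2 | 3 | repeat | stop patient | yes |

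The action is milder for the better-supported event in 4 of 6 combinations and equal in 2 of 6.

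**Step 3. Size for one patient.** At grade 2, 'Possibly' withholds up to 3 weeks x 1 infusion per week = 3 infusions. Section 7.3 then withdraws the patient if "Protocol treatment has to be delayed for more than 3 weeks". 'Unlikely' gives those infusions, assuming the category is not revised in the meantime. In Part 1 the next dose is between 720/660 = 1.09 and 60/12 = 5 times the last one. These are the planned steps of section 8.1.1. The table does not create them; it only decides whether the step is taken.

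**Step 4. Test the remedy.** Under the wording proposed below, cell 3 becomes 'Possibly', and the difference in Step 2 falls to 0 of 6. Cell 5 becomes 'Probably'. Cells 1, 2, 4 and 6 do not move, so no event is downgraded.

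**The case against.** Four arguments limit the point.

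**The footnote may already cover it.** It names the criterion and not a row, and marking a repeated phrase once is common. That is a fair reading for cell 5. It does not clearly reach cell 3, because the wording concerns the type of reaction, and a reversible event that has not improved yet is still one to which dechallenge applies.

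**The cell is nearly empty.** Participants are 40 to 80 years old, have Parkinson's disease and continue their usual medications (8.7). An assessor can often name another possible cause, and 'possible' is a weaker test than 'evident'. This stands: the case should be rare. A lenient assessor could also choose 'Possibly' anyway, but that relies on the reader to repair the table.

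**The matrices do not execute themselves.** Section 11.3 calls 8.3 guidance. Section 1.6 says "Decisions to pursue the trial for each patient will be taken unanimously by the three members", which includes an independent member. Investigator and sponsor both assess causality, and 7.3 allows withdrawal on medical judgement. A reader might infer from the inversion that such patients would in fact be escalated. The documents do not support that, since each safeguard can prevent it. They are discretionary, however, and leave the written category as it is.

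**Grade 3 and laboratory events are less exposed than they look.** With one narrow exception, an SAE stops the patient whatever its causality, and many grade 3 events would qualify as serious. A reader might also point to Part 1 laboratory abnormalities, which are first seen 3 days after infusion (9.2.1) with no repeat test listed at the next treatment visit (9.3.3). There, improvement is unknown, not absent. An untreated finding without symptoms would usually be grade 1 under the intensity table, where the action does not differ. It shows that the table is silent on unknown improvement, but it is not an instance of the inversion.

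**Conclusion.** The point holds in a narrow form. For a non-serious grade 2 or 3 event with a temporal relationship, no improvement where improvement could be expected, no other possible cause and no other proof, the printed rule is inverted. It is milder than for the same event with a competing cause at both grades and in both parts, and it conflicts with the opening principle of 8.3.

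This rests on a literal reading of the table and on the footnote not extending to reversible events that have not improved yet. How often the combination would arise cannot be derived from the protocol; it is expected to be rare. The safety management plan, which is not shown, may say more. The text supports a correction of the written rule. It does not support a claim that the trial's safety oversight fails.

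**What to change.** Amend the table and footnote in 10.1:

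- Define 'Possibly' as any event with a temporal relationship that does not meet 'Probably' or 'Definitely', whether or not another cause is possible.
- Limit 'Unlikely' to assessable events without a plausible temporal relationship. Keep 'Not related' as it is.
- Attach the dechallenge footnote to the 'Probably' row as well.
- State that an event whose improvement is absent or not yet assessable at the weekly decision is rated at least 'Possibly'.

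'Unlikely' should not be redefined by a more likely other cause. That would move some events now rated 'Possibly' down to continued dosing, and would loosen protection in a commoner situation than the one being repaired.

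The cost is one table and one footnote, with the same wording carried into the safety management plan and the eCRF, and a few more delays or single-patient stops. One consequence needs the sponsor's confirmation. With the footnote on 'Probably', an unresolved grade 3 event in Part 1 with no other cause evident, of a kind to which dechallenge does not apply, would reach the matrix row that stops all patients.
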